#### Analysis of primary and secondary outcomes

Generalized linear model (GLM) will be used to compare continuous primary and secondary endpoints, and further adjustment for age, gender, BMI and femoral artery calcification will be performed by multivariate GLM analysis. Logistic regression using generalized estimating equations (GEE) will be applied to compare categorical primary and secondary endpoints. Using multivariate GEE models, the subsequent analysis will be adjusted for age, gender, BMI and femoral artery calcification. The access-related complications are counted and analyzed by the number of femoral accesses instead of the number of patients.

To address heterogeneity among study population, pre-specified subgroup analyses will be performed in the following populations: heavily calcified femoral artery vs. lightly calcified femoral artery, tortuous iliac artery vs. non-tortuous iliac artery, obesity or overweight vs. normal weight, smoking vs. none, elderly or octogenarian vs. younger population.

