**Method:**

The SWEET study is a randomized, controlled, single-blind, single-center non-inferiority trial with two parallel groups in two cohorts respectively. After eligibility screening, subjects who meet the inclusion criteria will be divided into Cohort EVAR or Cohort TEVAR according to clinic interviews. And then participants in two cohorts will be randomly allocated to either intervention groups receiving percutaneous access endovascular repair or controlled groups receiving cutdown access endovascular repair separately. Primary clinician-reported outcome (ClinRO) is access-related complication, and primary patient-centered outcome (PCO) is time back to normal life. Follow-up will be conducted at 2 weeks, 1 month, 3 months postoperatively.

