#### Primary outcomes

The primary ClinRO endpoint is access-related complications assessed in-hospital, 2 weeks and 1 month after surgery. The definition of access-related complications includes

Access-site infection: inflammation of the groin presenting redness, swelling or exudation and requiring consecutive oral or intravenous antibiotics therapy.Bleeding/hematoma: fresh oozing blood or old blood stains seen on wound dressing/blood accumulation around the access site.Access-related arterial injury: arterial injuries requiring endarterectomy or patching due to the access technique.Femoral artery occlusion: femoral artery thrombosis presenting as distal artery pulse poorly requiring thrombectomy.Pseudoaneurysm: false aneurysm at the site of arterial injury presenting as a painful and pulsatile mass.Lymphorrhagia/seroma: swelling at access site caused by damage to lymphatic duct during access obtaining.Access-related nerve injury: nerve injuries presenting as persistent paresthesia of the thigh due to the access technique.Wound dehiscence: a partial or complete separation of previously close access wound edges.

The primary PCO endpoint is time (days) back to normal life/work assessed at 2 weeks by telephone interview and checked at 1 month and 3 months in outpatient clinics after surgery. To determine the outcomes that patients care most, we conducted a preliminary survey in 50 patients who received EVAR or TEVAR prior to our trial, and recovery time back to normal life or work represented the major PCO endpoint.

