#### Withdraw and dropout

Patients who agreed to participate in the trial can quit the study at any time for any reason without any consequences. After withdrawal, the subjects will not be replaced by others and their randomization number will not be re-used. Subjects are considered as dropout if they are lost to follow-up within 1-month postoperatively or they withdraw from the study.

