### Statistical methods

#### Analysis population

As Cohort EVAR and Cohort TEVAR were powered and randomized separately, the statistical analysis of both cohorts is planned to be reported separately. The analysis populations of this trial involve modified intention-to-treat (ITT) and per-protocol (PP) populations. The modified ITT is determined after randomization and when the patient started endovascular aortic repair, hence all patients who indeed receive endovascular aortic repair are involved in the primary analysis within the respective access group as originally allocated. In this trial, the modified ITT will be the main analysis set for the summary of both ClinROs and PCOs data. Both ITT and PP analysis are required for test of non-inferiority, and PP analysis serves as a sensitivity analysis. The non-inferiority margin was predetermined at 10%, and the non-inferiority test will be evaluated as a two-sided test at alpha = 0.05. When non-inferiority is reached, ITT is further tested for superiority.

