#### Handing of missing data

Missing data for baseline covariates will be addressed by multiple imputation in overall adjusted analyses, but those patients will not be included in the corresponding subgroup analysis.

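### Time back to normal life, a primary outcome observed only to 3 months, is fixed for a GLM on days with no censoring and no rule for patients not recovered at last contact

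*Protocol article*

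**What the plan says.** - **Outcome.** Primary outcomes defines the patient-centred endpoint as "time (days) back to normal life/work assessed at 2 weeks by telephone interview and checked at 1 month and 3 months".
- **Horizon.** The abstract states: "Follow-up will be conducted at 2 weeks, 1 month, 3 months postoperatively". Table 1 shows no later visit. Duration of access-related pain, a secondary outcome in days, follows the same schedule.
- **Analysis.** Analysis of primary and secondary outcomes says "Generalized linear model (GLM) will be used to compare continuous primary and secondary endpoints", then "Logistic regression using generalized estimating equations (GEE) will be applied to compare categorical primary and secondary endpoints". Access-related complications are categorical, so the recovery time is the only primary endpoint the GLM sentence can refer to. No time-to-event method is named anywhere.
- **Missing values.** The one rule is "Missing data for baseline covariates will be addressed by multiple imputation in overall adjusted analyses". It does not reach outcomes.
- **Dropout.** "Subjects are considered as dropout if they are lost to follow-up within 1-month postoperatively", or if they withdraw. The recovery time is followed for two months beyond that limit.
- **Analysis set and margin.** Analysis population makes modified ITT the main set for both types of outcome. The same paragraph says "The non-inferiority margin was predetermined at 10" per cent, without naming an endpoint.

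**The concern.** A recovery time with a fixed end of follow-up is right-censored for anyone not yet recovered when last seen: unrecovered at 3 months, or dead or lost before recovering. A GLM on days needs a number for every patient. A gamma or log-link version handles skewness but not censoring. The analyst must therefore leave these patients out, which contradicts the modified ITT set and conditions on recovery, or assign a value under a rule the plan does not contain. That choice can change the answer for a primary endpoint and could be made after the data are seen.

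The hypothesis is open in the same way. The trial is described throughout as non-inferiority, with a later test for superiority. The plan does not say which of the two applies to the recovery time, or on what scale.

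**Working it through.** **1. What the margin belongs to.** The sample-size section gives, for Cohort EVAR, complication rates of 7.64% (percutaneous) and 11.81% (cutdown), a margin of 0.10 and 80% power. The normal-approximation formula is n = (z_alpha + z_power)² × [p1(1−p1) + p2(1−p2)] / (margin + p_cutdown − p_percutaneous)².

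With one-sided 5%: (1.645 + 0.842)² × (0.1042 + 0.0706) / 0.1417² = 53.8, so 54 per arm, as stated. The same formula with 8.5%, 8.7% and 0.15 gives 45 for Cohort TEVAR, also as stated. (The match needs one-sided 5%; two-sided 5% would give 69 and 57. That is a separate matter.) So 0.10 is a difference in complication proportions. The section says that no patient-centred data were available for sizing.

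**2. Who lacks a value.** Only patients unrecovered at last contact. Someone back to normal on day 20 who is lost or dies in month 2 already has a recorded time.

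**3. Effect of dropping the unrecovered.** The documents give no recovery distribution, so the following is assumed: exponential times with a share s unrecovered at day 90, hence 1/λ = −90/ln(s).
- Mean restricted to 90 days: (1 − s)/λ.
- Mean among those with a recorded time: 1/λ − 90s/(1 − s).

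| Unrecovered, faster vs slower arm | Restricted means (days) | Difference | Means of recorded times (days) | Difference | Attenuation |
|---|---|---|---|---|---|
| 15% vs 25% | 40.3, 48.7 | 8.4 | 31.6, 34.9 | 3.4 | 60% |
| 5% vs 15% | 28.5, 40.3 | 11.8 | 25.3, 31.6 | 6.3 | 47% |
| 1% vs 3% | 19.3, 24.9 | 5.5 | 18.6, 22.9 | 4.2 | 23% |
| 0.1% vs 1% | 13.0, 19.3 | 6.3 | 12.9, 18.6 | 5.7 | 10% |

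**4. Power.** Simulated with 54 per arm, two-sided 5%, complete follow-up to day 90 and 10,000 trials per row.

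| Unrecovered | t-test, unrecovered dropped | t-test, unrecovered set to day 90 | Log-rank with censoring |
|---|---|---|---|
| 15% vs 25% | 10% | 28% | 31% |
| 5% vs 15% | 27% | 58% | 62% |
| 1% vs 3% | 21% | 27% | 28% |
| 0.1% vs 1% | 49% | 53% | 54% |

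**5. A different shape.** Assume lognormal times, log-SD 0.6 to 1.0, a true time ratio of 0.75, and 2% to 20% of the cutdown arm unrecovered at day 90. Measured against the untruncated mean difference, dropping shrinks it by 15% to 71% and a day-90 cap by 5% to 50%. At log-SD 0.8 and 54 per arm, power falls from 37% to 25% with dropping as the unrecovered share rises. It stays at 40% to 43% with the cap and at about 40% with log-rank.

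**6. The coding rule alone can decide the result.** Suppose recoverers average 25 days in both arms and 5% vs 15% are unrecovered. Dropping gives a difference of 0. Capping gives (0.85 × 25 + 0.15 × 90) − (0.95 × 25 + 0.05 × 90) = 34.75 − 28.25 = 6.5 days.

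**The case against.** The strongest reply is that the harm comes from an unstated coding rule rather than from the GLM. With complete follow-up, setting unrecovered patients to day 90 makes the difference in means equal to the 90-day restricted mean difference, and the power lost against log-rank is about 3 points. This stands, and it limits the size of the point. It does not remove it, because the plan contains no such rule, and a day-90 value is not justified for someone lost unrecovered at, say, 6 weeks.

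Second, most patients may be back to normal well before 3 months. If all are, the bias is zero. This also stands; the documents do not settle it.

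Third, an article may leave detail to a fuller document. That would cover the coding of deaths, for example. But the article itself names the method for continuous primary endpoints, and that method has no place for a censored time.

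A reader might go further in two ways that the text does not support:
- That the protocol applies its 10% margin to a time in days. It does not say so. It leaves the margin unassigned in a paragraph covering both outcome types, and the sample-size section ties it to complications. The defect is an unstated hypothesis, not a misapplied margin.
- That everyone who dies or is lost after 1 month lacks a value. Those who had already recovered have one.

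**Conclusion.** The point holds in this form: a GLM on days is fixed for a primary endpoint that is right-censored at 3 months, with no censoring and no rule for patients unrecovered at last contact. Duration of access-related pain shares the gap. Confidence is high in the gap and low in its size.

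Under the exponential assumption, dropping such patients attenuates the difference by 47% to 60% when 5% to 25% are unrecovered, and by 10% to 23% when 0.1% to 3% are. Capping at day 90 with complete follow-up costs little. These figures illustrate what is at stake and do not predict this trial's result. It would be too strong to say that the GLM must shrink any true difference: attenuation is the usual result of dropping, but its size depends on an unrecovered share and a handling rule that the documents do not give. Because this is a primary endpoint and the remedy uses the same visits, it should be corrected before analysis.

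**What to change.** 1. In Analysis of primary and secondary outcomes, take time back to normal life/work and duration of access-related pain out of the GLM sentence. Analyse them as time-to-event: Kaplan-Meier with log-rank or Cox, or the restricted mean difference to day 90 with 95% CI. Choose one as primary. Covariate adjustment can be kept.
2. Censor patients not recovered at last contact or at 3 months, whichever is earlier, and state a rule for death before recovery.
3. In Analysis population, state that the non-inferiority margin concerns access-related complications only, and that the patient-centred primary endpoint is tested for superiority on its own scale.

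Cost: the Protocol amendments section lists adjustment of statistical methods among potential major amendments, so this needs an amendment notified to the ethics committee and competent authority. The case record form must hold the date of recovery and the date last known unrecovered, and the equivalent dates for pain. No new visits and no additional patients are needed.

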#### Sample size

As no previous studies reported PCOs, we used the incidence of access site complications to estimate the sample size of the SWEET trial. According to previous studies, the incidence of access site complications in percutaneous EVAR was 7.64%, compared with 11.81% in cutdown EVAR (13). We estimated the number of patients needed in this non-inferiority trial with non-inferiority margin of 0.10 (bilateral α 5%, power 80%) by PASS 15.0 software, and 54 patients are required for percutaneous and cutdown EVAR group, respectively. To allow for 10% drop out, 60 patients will be recruited per group, i.e., 120 for Cohort EVAR.

Previous TEVAR studies lacked solid data in above aspects, however, the relevant data of transcatheter aortic valve implantation (TAVI) can be used for reference due to their similar surgical approach (15). The incidence of access site complications was 8.7% in percutaneous TAVI and 8.5% in cutdown TAVI (16). The sample size was calculated with non-inferiority margin of 0.15 (bilateral α 5 %, power 80 %), 45 patients are required for percutaneous and cutdown TEVAR group separately. Fifty patients will be recruited each group allowing for 10% drop out, and the number of subjects in Cohort TEVAR is 100. Therefore, the total sample size of the SWEET trial is 220. The whole calculation process can be found in Supplementary Tables S3, S4 (Supplementary Material).

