#### Secondary outcomes

The secondary ClinRO endpoints will be assessed in-hospital, 2 weeks and 1 month postoperatively, involving

Operative time (minutes): defined as duration of whole EVAR or TEVAR procedure.Length of hospital stay (days): defined as the period of time a patient remains in hospital.30-day limb graft occlusion: defined as a complete limb occlusion regardless of symptoms or lumen stenosis of more than 50% detected by image examination within 30 days postoperatively (17).30-day overall complications: defined as all systemic or local complications within 30 days postoperatively, whether related to the access or not.30-day mortality: defined as all-cause deaths occurring in the intervention population within 30 days postoperatively.

The secondary PCO endpoints involve quality of life scores and duration of access-related pain, which will be assessed simultaneously with the primary PCO endpoint.

Quality of life scores: participants' perception of physical and mental health form various aspects over time, scored with European Quality of Life 5 Dimensions (EQ-5D) questionnaire.Duration of access-related pain (days): length of participants' unpleasant sensory and emotional experience associated with access wound.

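### Logistic GEE is prescribed for 30-day mortality and limb graft occlusion with no provision for an empty arm; its customary robust Wald test then calls any split of events against none significant

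*Protocol article*

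**What the plan says.** The Analysis of primary and secondary outcomes section of the protocol article assigns one method to all binary endpoints: "Logistic regression using generalized estimating equations (GEE) will be applied to compare categorical primary and secondary endpoints". It then adds covariates: "Using multivariate GEE models, the subsequent analysis will be adjusted for age, gender, BMI and femoral artery calcification". It does not say whether standard errors are robust or model-based, or whether the test is Wald or score. It gives no alternative for sparse data.

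The Secondary outcomes section lists two endpoints that may well be sparse. One is 30-day mortality, "defined as all-cause deaths occurring in the intervention population within 30 days postoperatively". The other is 30-day limb graft occlusion, for which the section gives this wording: "defined as a complete limb occlusion regardless of symptoms or lumen stenosis of more than 50% detected by image examination within 30 days postoperatively". No expected rate is given for either.

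The comparisons are small. Under Analysis population, "the statistical analysis of both cohorts is planned to be reported separately". Under Sample size, "60 patients will be recruited per group, i.e., 120 for Cohort EVAR" and, for the other cohort, "Fifty patients will be recruited each group allowing for 10% drop out, and the number of subjects in Cohort TEVAR is 100".

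**The concern.** A logistic model has no finite odds ratio when one arm has no events: the fitted log odds for that arm run towards minus infinity. With model-based standard errors the reported error explodes as well, so at least no false signal appears. The sandwich standard error does not grow. It stays near the value set by the arm that has events, so an arbitrarily large log odds ratio is divided by a standard error of about 1 or less. The test then mainly records whether one arm happened to be empty.

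At 50 or 60 patients per arm, with emergency rupture cases excluded under Eligibility criteria, an empty arm is a realistic outcome for death and possibly for limb occlusion. One chance death could then be reported as an overwhelmingly significant mortality difference between access methods.

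**Working it through.** **Inputs from the protocol article.** Logistic GEE for categorical endpoints; cohorts analysed separately; 54 evaluable patients per arm (EVAR) and 45 (TEVAR). The recruited numbers follow from the 10% dropout allowance: 54/0.90 = 60 and 45/0.90 = 50. The document states no error rate for these endpoints, so there is no figure of its own to reproduce.

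**Assumptions.** True risk p equal in both arms, from 0.1% to 5%; a two-sided 5% test (the document states a level only for the non-inferiority test); patient-level analysis; robust Wald test unless stated otherwise.

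**Step 1: why the statistic breaks.** In a two-arm model without covariates, the sandwich variance of the log odds in an arm with k ≥ 1 events is n/[k(n − k)]. For k = 1 and n = 60 this is 60/59 = 1.017. In an empty arm with fitted probability ε, each residual is −ε, so the variance is nε²/[nε(1 − ε)]², which tends to 1/n = 0.017. The standard error of the log odds ratio is therefore at most √(1.017 + 0.017) = 1.017, however far the estimate has run.

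**Step 2: fits to k events versus none** (statsmodels GEE, binomial family).

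| Data | Log OR | Robust SE | Robust Wald p | Fisher p |
|---|---|---|---|---|
| 1/60 v 0/60 | 21.5 | 1.01 | about 1e-100 | 1.00 |
| 2/60 v 0/60 | 22.2 | 0.72 | about 3e-209 | 0.50 |
| 1/50 v 0/50 | 21.7 | 1.01 | about 4e-102 | 1.00 |

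For 1/60 v 0/60, other tests of the same GEE give very different answers. A model-based Wald test has a standard error of about 46,000 and p = 0.9996. A score test gives p = 0.315.

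**Step 3: how often this happens under equal risk.** With q = (1 − p)^n the chance that one arm is empty, the chance that exactly one arm is empty is 2q(1 − q). For n = 60 and p = 1%, q = 0.99^60 = 0.547, and 2 × 0.547 × 0.453 = 0.496. Enumerating all event pairs adds the few rejections where both arms have events:

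| True risk in both arms | 50 per arm | 60 per arm |
|---|---|---|
| 0.1% | 9% | 11% |
| 0.5% | 35% | 38% |
| 1% | 48% | 50% |
| 2% | 46% | 42% |
| 3% | 34% | 27% |
| 5% | 14% | 9% |

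Fisher's exact test stays at or below about 1% throughout. At the evaluable sizes of 45 and 54, the robust Wald test rejects 46% and 49% of the time at 1% risk.

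**Step 4: simulated GEE fits,** 400 trials per setting, 60 per arm, at risks of 0.5%, 1%, 2% and 3%. The robust Wald test rejects 36%, 50%, 41% and 25% without covariates, and 36%, 51%, 42% and 26% with four. Over both arm sizes the model-based Wald test never rejects and the score test rejects at most 3.5% of the time.

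**Step 5: primary composite.** At a common risk of 7.64% (the planned percutaneous EVAR rate), the same enumeration gives 3.4% with 60 units per arm and 4.3% with 120. At 10% it gives 3.3% and 4.5%. There is no inflation.

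**The case against.** The strongest objection is that the article names only a model family. The variance estimator, the test statistic and a zero-cell rule commonly sit in an analysis plan, which is not shown. A score test within GEE would remove the false signal. This stands as a limit on the claim: the inflation belongs to the robust Wald test, not to GEE as such. It does not dispose of the point. The article assigns this method to these endpoints without exception, and an analyst who follows it with customary output gets a spurious p-value. Switching to model-based errors gives an estimate nobody can use.

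A second objection is that no event rates are given, and that limb occlusion is defined broadly enough, including stenosis above 50%, that it may not be rare. That also stands; the rejection rate is therefore shown over a range. A third is that an odds ratio in the billions would be noticed before publication. Perhaps, but the plan names no alternative for that case.

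A reader might go further and infer that the plan carries a false-positive rate of 30-50% outright, that the primary endpoint is compromised, or that covariate adjustment makes matters worse. The documents do not support these. The first needs both the robust Wald test and an assumed risk of roughly 0.5-2.5%. The second is contradicted for the unadjusted composite at its planned rates. For the rare endpoints, adding four covariates changed the simulated rejection rates hardly at all.

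**Conclusion.** The concern holds in conditional form. For 30-day mortality and 30-day limb graft occlusion, the prescribed logistic GEE has no sound behaviour when one arm is empty. With the customary robust Wald test, any split of events against none is called significant. The resulting false-positive rate is about 35-50% at assumed true risks of 0.5-2%, 27-34% at 3%, and 9-14% at 0.1% or 5%, against a nominal 5%.

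This rests on three things the document does not state: the robust Wald test, the event rates, and a 5% level for secondary endpoints. It also assumes that the iteration runs far enough. If the fit for 1/60 v 0/60 stopped with the empty arm's log odds at −6, z would be 1.89 and the test would not reject; at −8, z would be 3.86.

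The problem is confined to rare secondary endpoints. It does not touch the unadjusted primary composite at its planned rates.

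**What to change.** In the Analysis of primary and secondary outcomes section, name 30-day mortality and 30-day limb graft occlusion in advance as exceptions to Wald-based logistic GEE. Compare them at patient level by an unadjusted risk difference, with a score (Miettinen-Nurminen) or exact interval and Fisher's exact test. If an adjusted estimate is wanted, specify Firth-penalised logistic regression. Keep GEE for the access-level primary composite, where the clustering of accesses within patients calls for it. Naming the endpoints beforehand is preferable to switching method on an observed event count.

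The change is one of wording and needs no further patients or data. The cost is that exact tests are conservative, and that the rarest endpoints are reported mainly without adjustment.

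### The non-inferiority margin is an absolute risk difference, but the only analysis named for the primary binary endpoint is logistic GEE, whose odds ratio does not map directly onto it

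*Protocol article*

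**What the plan says.** Under Sample size, the EVAR cohort is planned with a "non-inferiority margin of 0.10 (bilateral α 5%, power 80%) by PASS 15.0 software", from these rates: "the incidence of access site complications in percutaneous EVAR was 7.64%, compared with 11.81% in cutdown EVAR". For TEVAR: "The sample size was calculated with non-inferiority margin of 0.15", with rates borrowed from transcatheter valve implantation: "The incidence of access site complications was 8.7% in percutaneous TAVI and 8.5% in cutdown TAVI". The resulting sizes are 54 and 45 patients per group, raised to 60 and 50 for 10% dropout.

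Under Analysis population: "The non-inferiority margin was predetermined at 10%, and the non-inferiority test will be evaluated as a two-sided test at alpha = 0.05". No effect measure is attached to the 10%.

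Under Analysis of primary and secondary outcomes: "Logistic regression using generalized estimating equations (GEE) will be applied to compare categorical primary and secondary endpoints". A later model adjusts for age, gender, BMI and femoral artery calcification. Complications are counted per femoral access, not per patient. No other analysis of the primary binary endpoint is named.

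**The concern.** A non-inferiority conclusion needs an estimate and a confidence limit on the same scale as the margin. Here the margin sits beside proportions and the model reports an odds ratio. Nothing in the article links the two: there is no identity-link model, no standardisation of the logistic predictions, no odds-ratio margin and no reference control rate for a conversion.

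The analyst therefore has to choose. If the margin is converted to an odds ratio, the threshold depends on the control rate used. If the odds ratio is converted to a risk difference, the method must be chosen. With the small event counts expected here, these choices can give opposite answers on the same data.

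**Working it through.** **Inputs.** All are from Sample size. EVAR: percutaneous rate pT = 0.0764, cutdown rate pC = 0.1181, margin M = 0.10, n = 54 per group. TEVAR: pT = 0.087, pC = 0.085, M = 0.15, n = 45. Power is 80%.

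**Step 1: which scale is the margin on?** The unpooled risk-difference formula is

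n = (z_α + z_β)² × [pT(1−pT) + pC(1−pC)] / [M − (pT − pC)]²

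At one-sided 5%, (1.645 + 0.842)² = 6.183.

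- EVAR: 6.183 × (0.07056 + 0.10415) / 0.1417² = 53.8, rounded up to 54. With dropout, 54/0.9 = 60.
- TEVAR: 6.183 × (0.07943 + 0.07778) / 0.148² = 44.4, rounded up to 45. With dropout, 45/0.9 = 50.

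Both stated sizes reproduce exactly. Reading the EVAR margin as an odds ratio of 1.10 would need 442 per group. The margins are therefore absolute risk differences. (The match is at one-sided 5%; at one-sided 2.5% the formula gives 69 and 57. How that squares with the stated bilateral 5% is a separate question.)

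**Step 2: what odds ratio does the margin correspond to?** OR = [(pC + M)/(1 − pC − M)] / [pC/(1 − pC)].

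| Control rate | Margin | Equivalent OR |
|---|---|---|
| 11.81% (EVAR plan) | 10 points | (0.2181/0.7819)/(0.1181/0.8819) = 2.08 |
| 5% (assumed) | 10 points | (0.15/0.85)/(0.05/0.95) = 3.35 |
| 20% (assumed) | 10 points | (0.30/0.70)/(0.20/0.80) = 1.71 |
| 8.5% (TEVAR plan) | 15 points | (0.235/0.765)/(0.085/0.915) = 3.31 |
| 8.5% (TEVAR plan) | 10 points | (0.185/0.815)/(0.085/0.915) = 2.44 |

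In the other direction, a fixed OR of 2.08 allows 4.9 points at a 5% control rate (5% rises to 9.9%) and 14.2 points at 20% (20% rises to 34.2%).

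**Step 3: can the choice change the conclusion?** Take 4/54 percutaneous and 6/54 cutdown events, close to the planned rates, with patients as independent units.

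- Risk difference: −3.7 points, SE 5.57 points. Upper 95% limit = −3.7 + 1.96 × 5.57 = 7.2 points. This passes 10.
- Odds ratio: (4/50)/(6/48) = 0.64. SE of the log OR = √(1/4 + 1/50 + 1/6 + 1/48) = 0.676. Upper 95% limit = 0.64 × exp(1.96 × 0.676) = 2.41. This fails 2.08.

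Score intervals give about 8 points and an OR of about 2.3, so the disagreement is not an artefact of the Wald method. With z = 1.645 in place of 1.96 this particular table no longer conflicts, but others do: 5/54 against 6/54 gives 7.7 points (passes) and OR 2.33 (fails).

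**Step 4: which test does the sample size support?** If non-inferiority were tested against OR 2.08, the distance on the log scale from the planned OR of 0.618 is 1.216. The SE at 54 per group is √[(1/0.07056 + 1/0.10415)/54] = 0.664. Power is Φ(1.216/0.664 − z): 57% at one-sided 5% and 45% at one-sided 2.5%. On the risk-difference scale it is 80% and 70%.

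Steps 3 and 4 count patients. The plan analyses femoral accesses and gives no number of accesses per patient, so these steps show the effect of the scale. They do not forecast the trial's own limits.

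**The case against.** The strongest reply has three parts.

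First, a logistic GEE can deliver a risk difference by averaging its predicted risks under each access type. This is right. A reader might infer that the odds ratio can never be set against the margin; the correct statement is that it does not map directly and that the plan names no route.

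Second, the article never says that the odds ratio is the non-inferiority statistic. The test is described under Analysis population and the model in the next section, and the interval method could sit in a statistical analysis plan that is not shown. This also has force, and the power figures in Step 4 are conditional on a test that the article does not state. It does not remove the point. The article does name a model for this endpoint, and that model's natural effect measure differs from the scale of its own margin. A later plan that follows the named model inherits the mismatch.

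Third, two further criticisms are tempting and should not be made grounds for this point.

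- A reader might infer that the stratification factors are ignored, because the first model is unadjusted. The next sentence of the section adjusts for age and BMI among other covariates.
- A reader might infer that the adjusted model is far too large for the expected events. The patient-level counts at the planned rates are about 10.5 in EVAR (54 × 0.1945) and 7.7 in TEVAR (45 × 0.172). The analysis counts accesses, the rates are borrowed, and the adjusted model is described as coming after the main comparison. The documents do not establish that it is unworkable.

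**Conclusion.** The point holds in this form: the margins are absolute risk differences, the only analysis named for the primary binary endpoint is on the odds-ratio scale, and no link between them is specified. Ten points corresponds to an odds ratio anywhere from 1.71 to 3.35 as the control rate runs from 20% to 5%, and data near the design assumptions can pass on one scale and fail on the other.

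The conclusion rests on two things. The absolute scale is inferred from the exact reproduction of 54 and 45 per group, since the article does not name it. The 5% and 20% control rates are assumed, to show the range. The documents do not support saying that a logistic GEE is unusable for non-inferiority, or that the sponsor has committed to judging non-inferiority on the odds ratio.

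**What to change.** State that non-inferiority in each cohort is judged on the risk difference, percutaneous minus cutdown, and that it is concluded if the upper limit of the two-sided 95% interval lies below that cohort's margin. Then settle the unit:

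- If the femoral access stays the unit, estimate the risk difference by GEE with an identity link, or by standardised predictions from the logistic GEE. Cluster the variance by patient and include the stratification factors age and BMI. Name one of the two estimators in advance.
- If the patient becomes the unit, as in the sample size, say so explicitly, since this changes the stated analysis. Use a score interval for the risk difference stratified by age and BMI.

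Keep the odds ratio and the four-covariate model as supportive analyses. The rule needs one margin per cohort, so the 0.15 for TEVAR under Sample size and the single 10% under Analysis population must be reconciled at the same time.

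The cost is a few sentences and a few lines of code, with no change to data collection. The planned per-group sizes already rest on the risk-difference scale, so this change of scale does not alter them. It should be fixed before any unblinded look at the primary outcomes, including the planned interim analysis.
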